Smoking is a strong predictor of spontaneous preterm labor. Smoking during pregnancy has been associated with numerous adverse outcomes, including low birth weight, intrauterine growth restriction, prematurity, and infant mortality, due to heightened levels of inflammation and oxidative stress [4]. It is important to emphasize that smoking may be considered as a modifiable risk. In an epidemiological study based on national databases in the United States, Soneji et al. [4] observed that smoking cessation was associated with a relative reduction in the risk of PTB up to 23%, especially if the habit was stopped early in pregnancy. The authors also observed a dose-responsedose–response effect, with the risk of PTB being directly proportional to the number of cigarettes consumed. There are currently some strategies available to control smoking, such as pharmacological treatment, group support, and acupuncture. Studies suggest that auricular acupuncture can contribute to combating smoking through points that promote a reduction in anxiety and withdrawal symptoms [5].

Healthy vaginal microbiota is mainly colonized by *Lactobacillus* spp., which synthesizes lactic acid and other products that provide local protection against pathogens [6]. The replacement of the lactobacilli by anaerobic pathogens facilitates its ascent to the amniotic cavity and triggers an inflammatory response characterized by the production of cytokines and prostaglandins, ultimately inducing the labor-related events of myometrial contractility, cervical effacement, and rupture of the amniochorion membranes [7]. Although treatment for vaginal dysbiosis has not yet been proven effective in preventing PTB in late pregnancy, the condition is easily diagnosed by bacterioscopy, and the maintenance of eubiosis from the early stages of pregnancy may favor timely, adequate outcomes.

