Another well-established risk factor for PTB is the length of the uterine cervix. A cervical length of less than 25 mm between the 16th and 24th gestational weeks is a strong independent predictor of spontaneous PTB. The risk of PTB in these cases is estimated at 25–30% in women with no history of PTB and up to 35% in pregnant women who have previously presented PTB. If the length is under 15 mm, the risk of PTB reaches 50%. In fact, several authors indicate the need for screening cervical length in this period via transvaginal ultrasound [8,9]. The management of cervical shortening (CS) includes the topical administration of progesterone, the use of pessary, and cerclage. A recent meta-analysis detected a significant reduction in the rate of extreme prematurity (< 33 weeks of gestation, < 2,500 grams birth weight) in pregnant women with CS (< 25 mm) who used intravaginal progesterone daily [9].

A common factor for the aforementioned conditions is the possibility of implementing preventive measures. Identifying risk factors for PTB early and before the development of irreversible clinical symptoms (e.g. cervical dilation, intraamniotic infection, oxidative damage associated inflammation) enables a personalized approach to patient care, aiming to reduce the risk of preterm birth and its sequelae. Thus, the primary aim of this study protocol is to reduce PTB in pregnant women from Health Units in the city of Jaú - SP, Brazil by implementing a low-cost bundle to assess and manage major modifiable risk factors for PTB. The secondary aim is to demonstrate the feasibility of our implementation protocol.

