## Methods

### Study design

This is the protocol of an ongoing implementation study with a quasi-experimental controlled trial design conducted with pregnant women from primary health care units in the municipality of Jaú. The city of Jaú, located in the central region of the state of São Paulo, has a population of 151,881 inhabitants and 16 Basic Health Units (UBS) and Family Health Units (USF), in addition to a high-risk pregnancy clinic, Gestar, where this project is implemented.

The 16 UBS/USF were considered clusters and will be included in the study at different stages, according to the stepped wedge model, in which the clusters are gradually transferred to the intervention group at regular intervals until all have been transferred. This design is particularly useful in situations where the intervention cannot be implemented simultaneously for all units due to time, logistics, or ethical constraints [10]. In the first phase, eight of these clusters were randomly selected using a simple randomization process to receive the intervention, focusing on pregnant women during their first trimester. Over time, the remaining clusters will be randomly assigned to transition into the intervention group at regular intervals, using the same simple randomization method, ensuring that by the end of the study, all clusters will have received the intervention (Figure 1). This approach allows for a structured, phased implementation of the intervention, accommodating logistical and ethical constraints, and enables the comparison between clusters that have and have not yet received the intervention during the initial stages of the study.

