Below is a detailed description of each component of the intervention:(1) First Trimester (11 to 13 weeks and 6 days): Assessment and Smoking Intervention.**Sociodemographic and Clinical Assessment**: During the first trimester, participants undergo an initial interview to collect personal, social, and clinical information. This includes family and obstetric history, as well as smoking status.**Smoking Cessation Support**: Pregnant women identified as smokers who are willing to quit are provided with a comprehensive smoking cessation program. This includes referral to the city’s smoking prevention program, which is conducted at the Alcohol and Drug Psychosocial Care Center (CAPS-AD).The smoking intervention involves an initial interview and adjuvant treatment with auricular acupuncture. This technique uses pressure points in the ear to help reduce anxiety and withdrawal symptoms associated with smoking cessation.Acupuncture sessions are conducted every 15 days, where seeds are placed on specific points in the ear to stimulate them. Cotton and 70% alcohol are used to clean the ear, an auricular pressure gauge is used to locate the points, and mustard seeds with micropore are placed for acupressure of the selected points. The patients are instructed to stimulate these points themselves three times daily. Auriculotherapy is delivered by a trained and certified professional. Patient engagement is monitored by tracking attendance, with the number of appointments systematically recorded in the medical records.If necessary, group sessions with psychological support are provided at CAPS-AD, and pharmacological treatment, such as nicotine patches, may be used for gradual dose reduction to alleviate withdrawal symptoms.2. **Second Trimester (20 to 23 weeks and 6 days): Cervical Length Monitoring and Infection Treatment**.**Cervical Length Screening**: Between 20 and 24 weeks of gestation, all participating women undergo a transvaginal ultrasound to measure cervical length, a critical indicator of the risk for PTB.The measurement is taken with the patient in the lithotomy position, using a transvaginal probe to assess the distance between the internal and external orifices of the cervical canal. Women are instructed to empty their bladder before the ultrasound evaluation.Three consecutive measures are taken and the smallest value is considered. If a cervical length of less than 25 mm is detected, the woman is diagnosed with cervical shortening.Women diagnosed with cervical shortening are prescribed 200 mg of vaginal progesterone daily until 36 weeks of gestation, aiming to reduce the risk of PTB. For these women, the measurement is repeated biweekly for follow-up and monitoring treatment adherence.For cases of severe cervical shortening, such as lengths below 15 mm, cerclage – a surgical procedure to reinforce the cervix – is considered, depending on the patient’s clinical history and ongoing evaluations.**Investigation and Treatment of Infections**: During the same trimester, women are also screened for lower genital tract infections using molecular tests for *Chlamydia trachomatis* and *Neisseria gonorrhoeae*. These investigations are performed at this time due to the less friable nature of mid-trimester cervices in comparison to the first trimester of pregnancy.The assessment includes a complete gynecological examination with swabs for Gram staining, vaginal pH measurement, and cytobrush sampling collection for PCR analysis of cervical infection using the automated Cobas® 4800 CT/NG v2.0.Identified infections are treated according to the local clinical protocols to ensure the health of both the mother and the fetus.

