### Analysis plan

The main outcome of interest is gestational age at birth, based on first-trimester ultrasound, to be compared between the participants of the study and the general population. For the analysis, gestational age will be treated as categorical data (preterm birth vs. term birth). The primary analysis will follow the intention-to-treat principle: participants will be analyzed according to the assignment of their cluster at the time of inclusion. Secondary analyses will consider gestational age at delivery (continuous, in days) and other perinatal outcomes.

Secondary outcomes include the percentage of pregnant women included, the percentage of complete follow-up, percentage of adherence to prescribed treatments, and neonatal outcome (Apgar score, birth weight, and length of stay in the Intensive Care Unit). Descriptive statistics will be performed to analyze clinical, biological, and sociodemographic data of the studied population. Vaginal microbiota status across the trimesters will be compared using the Chi-square test.

Logistic regression will be performed to evaluate the role of the protocol in reducing PTB. To minimize multiplicity in the analysis and interpretation, covariates for adjustment such as parity, maternal age, and socioeconomic status will be included. The primary effect estimate will be obtained from mixed-effects logistic regression models including a random intercept for cluster and fixed effects for period and pre-specified baseline covariates (maternal age, parity, socioeconomic status). Additional per-protocol analyses will be performed as sensitivity analyses and will include participants who received the defined intervention components. Missing data in covariates will be handled using multiple imputations (MICE) under a missing-at-random assumption. The level of significance adopted for the tests used will be 5%, using *Prism* 5.0 (GraphPad Software).

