## Discussion

Several factors contribute to prematurity rates at a population level. Despite ongoing efforts to prevent prematurity, protocols for early identification and management of women at risk have not yet been fully defined or widely implemented. This is of particular importance in low‑ and middle‑income countries (LMICs), where the decision- makers are often insufficiently aware of populations health problems or face competing priorities that undermine investment in maternal – fetal health. In addition, population’s lack of awareness of the subject combined with financial and structural constraints further contributes to high PTB rates.

In the context of preterm birth (PTB) prevention, it is crucial to differentiate between merely identifiable risk factors and those that are manageable. Factors such as a personal or family history of PTB are inherently identifiable but cannot be altered. In contrast, modifiable risk factors, including smoking habit, vaginal dysbiosis, and cervical shortening, are more dynamic and can be managed through targeted interventions. These manageable factors are particularly responsive to intervention, meaning that timely and appropriate measures can significantly mitigate their impact on pregnancy outcomes, ultimately reducing the risk of PTB.

While individual interventions addressing these risk factors have been applied in some settings, to our knowledge, this is the first study to implement a low-cost bundle that systematically modulates modifiable risk factors for PTB in a high-prevalence population. Nevertheless, a limitation of our protocol is that the stepped-wedge quasi-experimental design may allow for confounding factors, such as selection bias by voluntary participation and possible cross-cluster contamination, despite the mitigation strategies described. This bundle is applied at multiple stages of pregnancy to address the specific modifiable risk factors of smoking, cervical shortening, and vaginal dysbiosis and infections. By providing tailored support, the bundle aims to lower the incidence of PTB within this cohort. The approach is practical, potentialy scalable to similar populations, and designed to be low-cost, making it suitable for implementation in resource-limited settings.

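### The primary model's covariate list leaves out first-visit smoking and previous preterm birth, two risk factors that the protocol itself names; this costs precision and protection against imbalance but does not invalidate the model

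*Protocol article*

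**What the plan says.** The Analysis plan takes the primary effect estimate from a mixed-effects logistic regression with a random intercept for cluster and "fixed effects for period and pre-specified baseline covariates (maternal age, parity, socioeconomic status"). The sentence before it is looser: "covariates for adjustment such as parity, maternal age, and socioeconomic status will be included". The sentence that defines the primary model, however, reads as a closed list of three.

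Elsewhere the article gives the reasons to look further:

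- Interventions, on the first-trimester interview: "This includes family and obstetric history, as well as smoking status".
- Background, on smoking: "Smoking is a strong predictor of spontaneous preterm labor".
- Background, on risk among women with a short cervix: 25 to 30% without a history of preterm birth and "up to 35% in pregnant women who have previously presented PTB".
- Discussion, on history: "Factors such as a personal or family history of PTB are inherently identifiable but cannot be altered".
- Study design, on allocation: "eight of these clusters were randomly selected using a simple randomization process to receive the intervention". The article describes no stratification.
- Discussion, on limitations: "the stepped-wedge quasi-experimental design may allow for confounding factors, such as selection bias by voluntary participation".

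**The concern.** A good adjustment covariate is fixed before the intervention, related to the outcome and available for every woman. Smoking at first contact and previous preterm birth meet the first two conditions by the protocol's own account, and for participants they are already recorded. Parity is not a substitute for history: a parous woman whose earlier birth was preterm and one whose earlier births were all at term receive the same value.

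The design gives two routes to imbalance. The first is chance, since only 16 units are allocated, by simple randomization. The second is selection. Women in activated units are invited, must consent and must attend the first two appointments to stay in the analysis. Random ordering of units does not protect against differences that arise in this way, and willingness to attend could plausibly be related to smoking or obstetric history. Baseline adjustment is a partial safeguard against both routes.

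Timing matters as well. The set is labelled as pre-specified, and a covariate added after outcomes are known would look data-driven.

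**Working it through.** **1. The plan's own figures.** The Study design section gives 201 women before clustering, m = 20, ICC = 0.01 and 20% loss.

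- Design effect: 1 + (20 − 1) × 0.01 = 1.19.
- 201 × 1.19 = 239.2, rounded up to 240.
- 240 / 0.80 = 300.

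These steps reproduce. The 201 is taken as given here; the sample size uses no covariates, so nothing in it changes.

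**2. Inputs for the illustration.**

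- Target effect, from the document: 18% − 11.5% = 6.5 points.
- Group size, assumed: 201 effective women split equally, 201 / 2 ≈ 101 per group.
- Prevalence p of previous preterm birth, assumed: 10%.
- Excess risk with that history: the document's only figures give 35 − 30 = 5 to 35 − 25 = 10 points, and only among women with a short cervix. A 20-point excess is added as an assumed upper case.

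**3. Chance imbalance in previous preterm birth.**

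- SD of the prevalence difference = √(2p(1 − p)/101) = √(0.18/101) = 0.042.
- At 1.96 SD: 0.083, or 8.3 points of prevalence.
- Shift in the crude rate difference = 0.083 × excess risk:

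| Excess risk | Shift at 1.96 SD | Share of 6.5 points |
|---|---|---|
| 5 points | 0.4 points | 6% |
| 10 points | 0.8 points | 13% |
| 20 points (assumed) | 1.7 points | 25% |

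With the 20-point excess, a prevalence of 5 to 15% gives 1.2 to 2.0 points. If each condition instead had 201 effective women, the SD would be √(0.18/201) = 0.030, and the three shifts would be 0.3, 0.6 and 1.2 points.

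**4. A second approach, on odds ratios (all inputs assumed except the 18%).** Hold the overall preterm rate at 18% and let the factor be 2 to 8 points less common in one condition. The shift is the imbalance times the risk gap implied by the odds ratio.

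- Smoking, prevalence 12%, odds ratio 1.3 to 2.0: 0.1 to 0.95 points (1 to 15% of 6.5).
- Previous preterm birth, prevalence 10%, odds ratio 2 to 4: 0.2 to 2.1 points (4 to 33% of 6.5).

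For 8 against 8 units of 20 women, the chance SD of a prevalence difference is about 3.7 to 5.6 points (prevalence 10 to 15%, ICC 0.01 to 0.05). Imbalances of 2 to 8 points are therefore ordinary.

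**5. Room in the model.** Expected events among 240 analysed women: 240 × 0.115 ≈ 28 to 240 × 0.18 ≈ 43. Eight units first and then two per month makes four further steps. With categorical periods and one term per covariate, the fixed effects are treatment 1 + period 4 + covariates 3 = 8. Events per parameter are 28/8 = 3.5 now and 28/10 = 2.8 with two more; at 43 events, 5.4 and 4.3.

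**The case against.** The case for leaving the list alone has several parts.

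- *Covariate choice is a judgement.* Age, parity and socioeconomic status form a defensible, short set, and nothing in the document requires more. This stands: the omission contradicts no other statement. It remains a weak choice, because the primary-model sentence closes the list without two factors that the article itself puts forward.
- *Chance imbalance under a randomized order is sampling variation, not bias.* This stands. The standard error already reflects it. The shifts above are also for a crude comparison; the random intercept, period effects and existing covariates may absorb part of them. Imbalance through voluntary participation is different, because randomizing units does not remove it.
- *The model has few events.* This stands as a cost, and it is the reason to add no more than two parameters.
- *The items are collected only in participants.* The interview is described as part of the intervention, and the article describes no equivalent for control women. Smoking taken from an interview in one condition and from records in the other could itself create bias. This limits how the fix is done. It does not defeat it, since age, parity and socioeconomic status must already be obtained for control women.

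A reader might infer that the protocol calls both factors strong predictors. It says so of smoking only. Previous preterm birth is named as a risk factor, and its collection is inferred from the reference to obstetric history.

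**Conclusion.** The point holds as an improvement worth making, not as an error that undermines the analysis. The primary covariate list omits two pre-intervention risk factors that the protocol names, in a design that it says is open to confounding. The loss is in precision (in a logistic model this shows mainly as power) and in protection against imbalance.

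On the document's own 5 to 10 point gap, a 1.96 SD imbalance in previous preterm birth is worth 0.4 to 0.8 points against the 6.5-point target. That gap applies to women with a short cervix; the excess risk among all women is not given. A reader might conclude that a quarter of the planned effect is at risk. That figure needs both an assumed 20-point excess and an imbalance at 1.96 SD, and the documents support neither as an expected value. A reader might also infer that the primary estimate would be invalid without these covariates. The documents do not support that either, because the order of the units is randomized and the model is otherwise coherent on this point.

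**What to change.** Before outcome data are analysed, amend the pre-specified covariates of the primary model:

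- Replace parity by a three-level factor: nulliparous; parous without a previous preterm birth; parous with a previous preterm birth.
- Add smoking at first prenatal contact (yes/no).
- Take both items from the same source in control and intervention women, for example prenatal records, so that measurement does not differ by condition.
- If smoking cannot be ascertained comparably, add only the history factor to the primary model and use smoking in a sensitivity analysis.
- State that smoking cessation, second-trimester cervical length and later microbiota findings are not adjusted for, because they follow the start of the intervention.
- Make the two sentences in the Analysis plan agree by removing the open-ended wording from the first.

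The cost is a change of wording, some record abstraction for control women, and one or two more parameters with about 28 to 43 expected events among 240 analysed.

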**Figure 1. f0001:**
[figure not shown]
Temporal flowchart of cluster inclusion (health units) in the quasi-experimental design study.

During the first 18 months, all first-trimester pregnant women from eight randomized UBS/USF (clusters) are being included. In the next step of the study, 2 UBS/USF per month will be included until all primary care units (clusters) in the municipality are included, as demonstrated in Figure 1.

All pregnant women of eligible gestational age from the eight initially randomized health units were systematically invited to participate in the study and referred to Gestar. Cluster randomization was performed using a randomization tool (https://www.random.org/). Allocation was concealed and known exclusively by the coordinating researcher until implementation, minimizing the risk of selection bias. All participants included in the study will be monitored until the gestational outcome through three appointments, one in each gestational trimester. The inclusion criteria for the study are singleton pregnancy and gestational age between 11 weeks and 13 weeks and 6 days at the first appointment, defined by ultrasound. Pregnancies with fetal death and those attending fewer than two study appointments (first and second trimester) will be excluded from the study.

Considering the intervention aims to reduce the preterm birth rate from 18% (baseline rate, DataSUS) to 11.5% (São Paulo state rate = target rate), with 95% confidence, 5% margin of error, and 80% statistical power, the minimum sample size calculated is 201 patients (SAS 3.0 software). Adjusting the sample size to account for cluster effects (DE = 1+(m − 1)×ICC, where DE: design effect; mean cluster size: *m* = 20; intra-cluster correlation coefficient: ICC = 0.01), the conventional individual-based sample of 201 increased to 240. Considering a 20% loss to follow-up, the final sample size will be 300 participants.

To reduce cross-contamination, clinical procedures are centralized at a reference site (Gestar), and the distribution of printed and digital protocols to the Health Units are restricted until activation. A 2-week operational wash-in with adherence monitoring was implemented.

This project was approved by the Research Ethics Committee of Unoeste – Universidade do Oeste Paulista (CAAE 63,623,922.70000.5515). All patients involved will be informed about the research and sign the informed consent form.

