
**3. Throughout All Trimesters (11 weeks to Term): Vaginal Microbiota Monitoring and Dysbiosis Management.**

**Quarterly Assessment of Vaginal Microbiota**: During each trimester, vaginal samples are collected from the vaginal wall using sterile swabs to assess eubiosis (the balance of the vaginal microbiota) by bacterioscopy using the Gram staining method according to the criteria set by Nugent et al. [11].The microscopic evaluation aims to identify dysbiosis, such as bacterial vaginosis, candidiasis, or other alterations in the vaginal microbiota. The trained examiner will be blinded to patients’ clinical symptoms and a quality assessment of the readings will be performed by an independent examiner, following the same criteria.Women diagnosed with dysbiosis receive treatment based on the type of condition identified. For bacterial vaginosis, standard antibiotic metronidazole 500 mg orally 12/12 h for 7 days regimens are administered. Recurrent cases are treated with metronidazole gel 0.75% 5 g intravaginally once a day for 5 days or Clindamycin cream 2% (20 mg/g) 5 g intravaginally at bedtime for 7 days, according to the CDC protocol, and the partner is treated with secnidazole orally 1000 mg, single dose.Standard antifungal treatment provided for candidiasis is topic nistatin for seven nights. Recurrent cases are treated with miconazole 2% cream 5 g intravaginally daily for 14 days.Additionally, all participants are educated on proper intimate hygiene practices to help maintain a balanced vaginal environment throughout the pregnancy.

This protocol is conducted alongside standard prenatal care and patients are periodically reminded of their appointments. The study protocol is original and was registered in the Brazilian Clinical Trial Registry (ReBec) on 29 October 2024 (approval pending).

Data regarding the appointments, patients’ compliance with the protocol, and pregnancy outcome will be collected through interviews and medical records by the researchers for subsequent analysis. Data entry will be double checked, periodically updated and securely stored in the institutional repository. Only the researchers will have access to individual-level data, while metadata will be made openly available after publication of the study results.

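### The primary analysis is called intention-to-treat, but included women can leave it through a two-appointment rule or a missing birth outcome, and the only missing-data rule covers covariates

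*Protocol article*

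**What the plan says.** Four statements in the Protocol article bear on this point.

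- **Analysis principle (Analysis plan).** The primary analysis is labelled intention-to-treat, in the sense that "participants will be analyzed according to the assignment of their cluster at the time of inclusion". The outcome is binary (preterm or term). The model is a mixed-effects logistic regression with a random intercept for cluster and fixed effects for period, maternal age, parity and socioeconomic status.
- **Missing data (Analysis plan).** The one rule given is "Missing data in covariates will be handled using multiple imputations (MICE) under a missing-at-random assumption". The only sensitivity analyses named are per-protocol.
- **Exclusion and loss (Methods, Study design).** Women who attend fewer than two study appointments (first and second trimester) are excluded from the study. The sample size section then states: "Considering a 20% loss to follow-up, the final sample size will be 300 participants".
- **Source of the outcome (Methods, Interventions).** Data on "pregnancy outcome will be collected through interviews and medical records by the researchers for subsequent analysis". The text does not say whether this is also done for women who stop attending.

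**The concern.** Intention-to-treat in a cluster design needs two things: each woman is counted under the condition of her cluster at inclusion, and included women are not removed because of what they do later. The plan states the first. The attendance rule works against the second, because a woman who was included at 11 to 13 weeks leaves the study if she misses the second-trimester appointment.

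A further group may attend both appointments and still have no known delivery date. With one binary outcome per woman, a logistic model drops her, and imputing covariates does not bring her back.

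The selection need not fall equally on the two conditions. The three appointments are described for women enrolled to receive the bundle. No matching attendance requirement is described for comparison women, and the Analysis plan also speaks of comparing participants with the general population. Losses tied to appointments would then act on the bundle side and not cancel.

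The direction is plausible from the article itself. The Background names smoking and previous preterm birth as linked to preterm birth, and neither is among the model's covariates. If they also make non-attendance more likely, which is an assumption, the women who remain are at lower risk and part of the apparent benefit comes from drop-out.

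**Working it through.** **Inputs from the plan (Methods, Study design).** "the conventional individual-based sample of 201 increased to 240"; "mean cluster size: *m* = 20"; "intra-cluster correlation coefficient: ICC = 0.01"; 20% loss; 300 final; and the aim to "reduce the preterm birth rate from 18% (baseline rate, DataSUS) to 11.5"%.

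**Reproducing the plan's figures.**
- Design effect = 1 + (20 − 1) × 0.01 = 1.19.
- 201 × 1.19 = 239.19, rounded up to 240.
- 240 / (1 − 0.20) = 300.
- Allowed loss = 300 × 0.20 = 60 women.
- Planned effect = 18 − 11.5 = 6.5 percentage points.

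The chain from 201 to 300 reproduces. Because 240 already discounts the 60, dropping them does not take the sample below plan. The issue is bias, not power.

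**Understatement of the bundle's rate.** Let p be the rate among retained women, f the fraction of included women with no outcome, and RR the risk ratio of lost versus retained women. Then:

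rate in all included = (1 − f) × p + f × RR × p, and understatement = f × (RR − 1) × p.

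Take p = 11.5% (the plan's target). RR is assumed, as the article gives no figure. f = 0.20 is the full allowance. f = 0.10 is an assumed case in which records recover half of the outcomes.

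| f | RR | Rate in all included | Understatement | Share of 6.5 points |
|---|---|---|---|---|
| 0.20 | 1.5 | 9.2 + 3.45 = 12.65% | 1.15 points | 18% |
| 0.20 | 2 | 9.2 + 4.6 = 13.8% | 2.3 points | 35% |
| 0.10 | 1.5 | 10.35 + 1.725 = 12.075% | 0.575 points | 9% |
| 0.10 | 2 | 10.35 + 2.3 = 12.65% | 1.15 points | 18% |

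**Mechanical limits at f = 0.20.** Events among 240 retained women = 240 × 0.115 = 27.6. If none of the 60 deliver preterm, the rate is 27.6/300 = 9.2%. If all do, it is 87.6/300 = 29.2%. The rate returns to 18% if (54 − 27.6)/60 = 44% of the 60 deliver preterm. These are limits, not expectations.

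**A milder, mechanism-based case.** Suppose loss depends only on smoking (assumed prevalence 15%, odds ratio for preterm birth 2) and previous preterm birth (10%, odds ratio 3), each factor doubling or tripling the risk of loss, with 20% lost overall. With a true rate of 11.5%, dropping lost women then lowers the observed rate by about 0.5 points (doubling) or 0.9 points (tripling).

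**Setting the passages side by side.** Study design removes a woman by attendance. The Analysis plan assigns her by cluster at inclusion and gives a missing-data method that does not reach the outcome. Interventions names medical records, a source that does not depend on attendance, but does not commit to using it for non-attenders. Nothing joins these statements into one defined primary analysis set.

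**The case against.** The strongest case against has four parts.

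1. *This is an omission from a condensed article.* A full protocol or analysis plan may handle missing outcomes, and a rule about covariates does not forbid imputing outcomes. This largely stands: a missing imputation model or tipping-point table would not be a finding alone. It does not dispose of the attendance exclusion, which is a stated rule that selects on behaviour after inclusion.
2. *The plan's definition of intention-to-treat only fixes the condition a woman counts under.* That is a fair reading of the sentence. But the label is normally understood to cover the analysis set too, and the attendance rule is the kind of exclusion a per-protocol set is meant to hold.
3. *Sixty women without an outcome is not a documented fact.* This stands. A reader might infer from the 20% allowance that 60 delivery dates will be unknown, or that records will not be searched for women who stop attending. The documents support neither. Loss to follow-up is not defined as an unknown birth outcome, some of the 60 may be women removed by the attendance rule, and medical records are a named source. Sixty is an upper planning figure.
4. *The size rests on assumed risk ratios and on one group's rate.* This also stands. One could compare the bias with the standard error of a single proportion, √(0.115 × 0.885 / 240 × 1.19) = 2.25 points, but the primary estimate is a between-condition contrast from a mixed model. That ratio should not be used to judge the effect on the trial's conclusion.

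**Conclusion.** The point holds in a limited form. The two-appointment exclusion conflicts with an intention-to-treat primary analysis as usually understood, and the stated missing-data rule does not cover the primary outcome. Followed as written, the primary model uses women selected by later attendance and outcome availability, and as described that selection applies to the bundle side.

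If lost women are at higher risk, the bundle's preterm birth rate is understated. The amount cannot be determined from the article: 1.2 to 2.3 points is an upper illustration (all 60 outcomes missing, risk ratio 1.5 to 2), and about 0.5 to 0.9 points follows from the milder assumptions above. The article does not show that 60 outcomes will be missing, nor that the result will be biased by any particular amount. The change is worth making because it is cheap and settles a written conflict about who is analysed.

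**What to change.** 1. **Reconcile Study design with the Analysis plan.** State that every included woman stays in the primary intention-to-treat set whatever her attendance, and move the two-appointment criterion to the per-protocol analysis. Both sections need editing: changing only the Analysis plan would leave the exclusion in force.
2. **Take the delivery date for all included women from medical records**, whether or not they still attend. The records are already a named source, and the first-trimester dating scan is available from inclusion.
3. **For outcomes still missing, state that the missing-data method covers preterm birth as well as covariates**, using cluster, period and baseline variables that are available in both conditions. Items collected only at bundle appointments cannot serve the comparison women.
4. **Report one simple sensitivity analysis** that raises the odds of preterm birth in women with a missing outcome in steps (for example 1.5, 2 and 3 times) and shows where the conclusion changes.

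Cost: a record search for women who stop attending, edits to two sections, a somewhat larger imputation model and one extra table. No additional participants or procedures are needed. The estimate may become less favourable or less precise.
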